# The effect of a vegan diet with or without resistance exercise on thigh muscle volume in older adults. Research protocol of the Vold-study: a 12-week randomized controlled trial

**DOI:** 10.1186/s12877-025-06708-9

**Published:** 2025-12-26

**Keywords:** Plant-based food, Animal-based food, Skeletal muscle, Muscle mass, Aging, Sustainable food

## Abstract

**Background:**

Plant-based diets are increasingly adopted. Plant-based foods exhibit a lower protein quantity and quality compared to animal-based foods. As such, a fully plant-based, i.e. vegan, diet may be suboptimal for the maintenance of skeletal muscle mass later in life. The primary objectives of this study protocol are therefore: (1) To assess the effect of a 12-week self-composed vegan diet in comparison to an omnivorous diet on thigh muscle volume in community-dwelling older adults; and (2) To assess the effect of a 12-week self-composed vegan diet combined with twice-weekly resistance exercise (RE) on thigh muscle volume in comparison to a vegan diet without RE in community-dwelling older adults.

**Methods:**

Seventy-two community-dwelling individuals aged ≥ 65 years with a BMI between 23 and 32 kg/m^2^ will be included in this randomized controlled trial. Eligible participants will be randomly allocated to either follow their habitual omnivorous diet, a self-composed vegan diet, or a self-composed vegan diet combined with two sessions of RE per week for 12 weeks. Participants will be guided through monthly nutrition information meetings. Dietary intake and physical activity levels will be assessed using food records and accelerometery. The primary study outcome will be thigh muscle volume, assessed at baseline and after 12 weeks using magnetic resonance imaging (MRI). Secondary outcomes will be: body composition, muscle fat infiltration, muscle strength, bone mineral density, bone turnover markers, metabolic profile, insulin levels, cobalamin, iron and vitamin D status, hs-CRP, gut metabolomics and metagenomics, gastro-intestinal symptoms and dietary intake. Measurements will take place at baseline, after 6 weeks, and after 12 weeks. Additionally, mixed muscle protein synthesis rates will be assessed during the first ten days of the intervention using a deuterium oxide protocol. Data will be analysed using independent t-tests and linear mixed models.

**Discussion:**

The results will provide valuable insights regarding the implications of consuming a vegan diet later in life for skeletal muscle and other health outcomes, and may contribute to the substantiation of the envisaged more plant-based dietary guidelines.

**Trial registration:**

The trial is registered at clinicaltrials.gov (NCT05809466; registered on 22 February 2023).

**Supplementary Information:**

The online version contains supplementary material available at 10.1186/s12877-025-06708-9.

## Introduction

Environmental and health concerns have led to a growing encouragement for consumers in high-income countries to adopt more plant-based diets [1–3]. Plant-based diets are classified based on the proportion and source of animal- and plant-based foods present in the diet. While a vegetarian diet excludes specific animal-based food groups, as meat and/or fish, a vegan diet represents the strictest form of a plant-based diet and excludes all foods from animal origin. Ample plant-based food consumption holds potential health advantages, including a reduced risk of obesity and cardiometabolic disease [4–8]. However, a strict vegan diet poses a risk for insufficient intake of several nutrients, particularly for protein, vitamin D, cobalamin, calcium, zinc and selenium [9, 10].

An increased risk of deficiency in several of the above-mentioned nutrients typically presents itself later in life as well. The consumption of protein and the status of vitamin D, calcium, and cobalamin have frequently been reported to be low in older individuals. Insufficiencies of these nutrients can lead to adverse effects, including, but not limited to, a reduction in muscle mass, an increased risk of hip fractures and the development of macrocytic anemia, respectively [10–13]. We previously suggested that a vegan diet elevates the risk of an inadequate protein intake in older individuals even further, which may accelerate the age-related decline in muscle mass and function and subsequently increase the risk of sarcopenia [10]. Sarcopenia refers to the age-related decline in muscle strength accompanied by a loss of muscle mass and/or function, typically commencing around the age of 50. It is estimated that up to 30% of older adults residing in community settings experience sarcopenia. Sarcopenic individuals experience an increased susceptibility to falls, hospitalization, and other complications. Adequate dietary protein intake of sufficient quality, particularly in conjunction with resistance exercise (RE), is an established approach in preventing sarcopenia [14].

The ingestion of dietary protein stimulates the growth of muscles through the upregulation of muscle protein synthesis (MPS) and the inhibition of muscle protein breakdown. The degree to which a protein source can promote muscle mass maintenance and accretion predominantly hinges on the quantity and the quality of the protein consumed. Protein quality pertains to the capacity of a protein source to fulfill its functions following digestion and absorption, such as the stimulation of MPS [15]. Plant-based foods are generally considered to have a relatively lower protein quantity and quality in comparison to animal-based foods. Plant-based foods frequently exhibit an incomplete amino acid profile. Additionally, the concurrent abundance of anti-nutritional factors and dietary fibers in plant-based foods further lowers their protein digestibility, and as such, the bioavailability of the essential amino acids within the protein [16, 17]. The lower protein functionality of a protein source that results from its low protein quality is particularly important for older individuals, considering the already blunted MPS response to protein intake typically seen later in life (i.e. anabolic resistance) [18, 19]. Illustrating this, the consumption of 30 g of wheat protein hydrolysate has been shown to increase MPS rates in young individuals, while a similar amount did not increase MPS in older individuals [20, 21].

We previously observed a substantial and significant difference in the post-prandial MPS response to a vegan meal when compared to an omnivorous meal in older adults [22]. On the other hand, these findings were not confirmed when a highly controlled vegan diet providing ample protein was consumed for several days by older adults in a recent study from our group [23], and in another study [24]. Although providing a high internal validity, these results do not reflect the impact a longer term, self-composed vegan die may have, as food, and as such nutrient, intake will be largely different. Furthermore, it remains largely unclear to what extent diet induced changes in mixed MPS affect the longer-term adaptations in muscle mass [25]. Both the acute and longer-term effects of consuming a *self-composed* vegan diet on muscle- and other health related outcomes in the later stages of life have yet to be fully understood.

Considering the high environmental impact of animal-based food production, and the concurrent demand for high-quality protein consumption later in life, it is urgently needed to assess the effects of a vegan diet on skeletal muscle and other health related outcomes in older adults. Thereby shifting from a highly controlled setting and testing isolated proteins and controlled diets [20, 22–24, 26], towards longer-term adaptations to a self-composed vegan diet. Additionally, strategies that may aid muscle maintenance in older individuals while consuming a vegan diet will have to be explored. Therefore, the current paper describes a protocol for a randomized controlled intervention trial with three parallel arms that aims to assess the effect of a self-composed 12-week vegan diet on skeletal muscle mass, strength, and other health related outcomes in comparison to (1) an omnivorous diet, and (2) in comparison to a self-composed vegan diet with concomitant RE, in community-dwelling older adults. We hypothesize that switching to a self-composed vegan diet for 12 weeks leads to a small decrease in thigh muscle volume in comparison to an omnivorous diet, and that concurrent RE will attenuate these losses. An overview of all study objectives is presented in Table 1.

**Table 1 Tab1:** Primary, secondary and explorative objectives of the Vold-study

**Primary objectives** •To assess the effect of a 12-week self-composed vegan diet in comparison to an omnivorous diet on thigh muscle volume in community-dwelling older adults. •To assess the effect of a 12-week self-composed vegan diet combined with twice-weekly RE on thigh muscle volume in comparison to a self-composedvegan diet without RE in community-dwelling older adults. **Secondary objectives** •To assess the effect of a 12-week self-composed vegan diet in comparison to an omnivorous diet in community-dwelling older adults on: -Other body composition components (fat distribution; (appendicular) lean mass); -Muscle strength; -Bone mineral density and bone turnover markers; -Metabolic profile; -Insulin levels; -Vitamin B12, vitamin D and iron status; -hs-CRP; -Gastro-intestinal symptoms; -Gut metabolomics and metagenomics. •To assess the effect of a 12-week self-composed vegan diet combined with twice-weekly RE in comparison to a self-composed vegan diet without RE in community-dwelling adults on: -Other body composition components (fat distribution; (appendicular) lean mass); -Muscle strength; -Bone mineral density and bone turnover markers; -Metabolic profile; -Insulin levels; -Vitamin B12, vitamin D and iron status; -hs-CRP; -Gastro-intestinal symptoms. •To assess the effect of a *10-day* self-composed vegan diet in comparison to an omnivorous diet on mixed MPS rates in community-dwelling older adults. •To assess the effect of a *10-day* self-composed vegan diet combined with twice-weekly RE in comparison to a self-composed vegan diet without RE on mixed MPS rates in community-dwelling older adults. •To assess the nutritional composition of a self-composed vegan diet consumed by community-dwelling older adults. **Explorative objectives** •To assess the effect of a 12-week self-composed vegan diet in comparison to an omnivorous diet, and in comparison to a self-composed vegan diet combined with twice-weekly RE in community dwelling older adults on: -Body mass; -Immune markers; -(Osteo)arthritis complaints in (osteo)arthritis patients; -DNA methylation.	

Abbreviations used: *RE* Resistance exercise, *MPS* Muscle protein synthesis, *hs-CRP* High sensitive c-reactive protein

## Methods and design

### Study design

#### Study overview

This study is an open-label, single-center, randomized controlled trial with three parallel study arms. A general overview of the design is presented in Fig. 1. The study duration for enrolled participants will be approximately 14 weeks. Following inclusion, the participants will be randomized to follow either their habitual omnivorous diet (OMNI), a self-composed vegan diet (VEG), or a self-composed vegan diet with concurrent resistant exercise twice a week (VEG-RE) for 12 weeks. All groups will be guided through monthly nutrition information meetings. Measurements to assess the study outcomes will be performed at baseline, after 10 days, after 6 weeks and after 12 weeks. Additionally, all participants will follow a deuterium oxide protocol during the first ten days of the intervention period to allow for the assessment of mixed MPS rates. A detailed description of all measurements can be found in the subsequent paragraphs. Measurements will take place at the hospital Gelderse Vallei (Ede, The Netherlands) and at the Human Nutrition Research Unit at Wageningen University and Research (Wageningen, The Netherlands). All study measurements will be performed according to strict standard operating procedures. The duration the study visits range from one to three hours. The study will be conducted in accordance with the Declaration of Helsinki and has been approved by the medical ethics committee Oost-Nederland (METC-Oost; NL82788.091.22). The trial is registered at clinicaltrials.gov (NCT05809466) and the SPIRIT 2013 checklist related to the manuscript can be found in supplementary Table 1.

**Fig. 1 Fig1:**
[figure not shown]
Study design. *Not in the VEG-RE-group. ** only in participants diagnosed with (osteo) arthritis at the moment of screening. Abbreviations: OMNI, the participants allocated to consume their habitual omnivorous diets; VEG, the participants allocated to consume a vegan diet; VEG-RE, the participants allocated to consume a vegan diet and participate in a resistance exercise program; MRI, magnetic resonance imaging; DEXA, Dual X-Ray Absorptiometry; D_2_O, deuterium oxide; GSRS, gastro-intestinal symptom rating scale; WOMAC, Western Ontario and McMaster Universities Osteoarthritis Index.

#### Sample size calculation

The sample size calculation was based on the primary outcome and was performed in GPower version 3.1.9.4 (Düsseldorf, Germany). Since the current study aims to compare the effect of a vegan diet to an omnivorous diet on thigh muscle volume, and to compare the effect of a vegan diet to a vegan diet in combination with RE on thigh muscle volume (two different contrasts), the sample size calculation was based on testing change in thigh muscle volume between two group comparisons. A separate two-tailed α-level of 0.05 was used for each contrast. A mean change of 4% in thigh muscle volume was expected in the vegan group. The latter was based on previous studies that assessed changes in thigh muscle volume during caloric restriction in middle aged to older adults, as no study has previously assessed the effect of a vegan diet on thigh muscle volume. Reductions in thigh muscle volume of ~ 6.5% were previously observed following a year of caloric restriction [27, 28]. Others additionally observed that the largest decline in thigh muscle volume presented itself during the first three months of caloric restriction [29]. Additionally assuming an expected reduction in the consumption of protein with a concurrent reduction in protein quality [10, 30], a mean change of 4% in thigh muscle volume was expected on the vegan diet in the present study. Using an expected mean change of 4% and standard deviation of 5% [10, 27–30], and 80% power, a total of 60 participants, 20 per group, will need to be included in the study. Considering a drop-out rate of 20%, 24 participants per group will be recruited, leading to a total of 72 participants.

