#### Randomization

Following inclusion, participants will be randomized to one of the three study arms on a 1:1:1 ratio, using block randomization with variable block sizes of 3, 6 and 9 to ensure equal allocation to each group. Randomization will be stratified for gender and partners will be randomized together. The randomization will be performed in Castor EDC by a member of the research team [31]. Considering the logistics of the study procedures, both the members of the research team and the participants will be aware of the group allocation.

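### The single 80% power statement does not hold for the exercise contrast: 20 per arm gives 69% even if exercise prevents the whole 4% loss, and less under the partial attenuation that the hypothesis allows

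*Protocol article*

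**What the plan says.** The article has two primary objectives on thigh muscle volume: VEG against OMNI, and VEG-RE against VEG. One calculation is meant to cover both. The sample size section says "the sample size calculation was based on testing change in thigh muscle volume between two group comparisons", and "A separate two-tailed α-level of 0.05 was used for each contrast".

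The only effect given is "A mean change of 4% in thigh muscle volume was expected in the vegan group". The section argues for it from muscle loss during caloric restriction and from an expected fall in protein intake and quality. It then computes: "Using an expected mean change of 4% and standard deviation of 5" per cent, "and 80% power, a total of 60 participants, 20 per group, will need to be included in the study". After that, "Considering a drop-out rate of 20%, 24 participants per group will be recruited". Allocation is equal: "participants will be randomized to one of the three study arms on a 1:1:1 ratio".

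No expected change is given for OMNI or for VEG-RE. The hypothesis at the end of the Introduction is that the vegan diet causes a small loss relative to OMNI and that "concurrent RE will attenuate these losses". The opening of the Discussion describes the exercise aim in the same terms.

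**The concern.** A change expected within one arm is a difference between arms only if the other arm does not change. Using 4 points for both contrasts therefore assumes zero change in OMNI and zero change in VEG-RE. The second assumption means that exercise prevents all of the loss. That is the upper limit of attenuation, and the article neither says so nor supports it.

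The exercise contrast is a primary question, not a secondary one. A reader of the section would take it to have 80% power under the stated hypothesis. If it does not, the article overstates what the trial can show on half of its primary aims.

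**Working it through.** **Inputs.** All are from the sample size section: difference 4 points, SD 5 points, two-sided α = 0.05, power 80%, 20 per arm, 24 recruited per arm, 20% drop-out. The planned test is the independent-samples t-test on change (statistical analysis section).

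**Step 1: reproduce the plan's 20 per arm.** The normal approximation is n = 2(z_α + z_β)²(SD/difference)².

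- Two-sided: 2 × (1.960 + 0.842)² × (5/4)² = 2 × 7.85 × 1.5625 = 24.5, so 25 per arm. The exact t-test gives 25.5, so 26.
- One-sided: 2 × (1.645 + 0.842)² × 1.5625 = 2 × 6.18 × 1.5625 = 19.3, so 20 per arm. The exact one-sided t-test has 79.9% power at 20.

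The stated 20 is not reproduced by the stated two-tailed test. Of the other variants tried, a paired two-sided t-test gives 15, a two-sided t-test at α = 0.025 gives 31, and a three-group ANOVA with means 0, −4, 0 gives about 71 in total. None gives 20 per arm.

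**Step 2: power at a full 4-point difference.** The noncentrality is (difference/SD) × √(n/2) = 0.8 × √10 = 2.53, and the two-sided critical value on 38 degrees of freedom is 2.02. Exact power is 69%. This uses the plan's own inputs, with exercise preventing the entire loss. The same 69% applies to VEG versus OMNI if OMNI does not change.

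**Step 3: power for other differences.** If VEG loses 4 points, attenuation confines the VEG-RE minus VEG difference to between 0 and 4. The article gives no share prevented, so every row except the second is an assumption. The 19 column comes from 24 × 0.8 = 19.2.

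| VEG-RE minus VEG | Meaning if VEG loses 4 | 19 per arm | 20 per arm | 24 per arm |
|---|---|---|---|---|
| 5 points | VEG-RE gains 1 point | 85% | 87% | 92% |
| 4 points | all of the loss prevented | 67% | 69% | 77% |
| 3 points | three quarters prevented | 44% | 46% | 53% |
| 2 points | half prevented | 22% | 23% | 27% |

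For 80% power, differences of 4, 3 and 2 points need 26, 45 and 100 analysed per arm.

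**Step 4: the difference that 80% power requires.** It is 4.55 points at 20 per arm and 4.13 points at 24. With VEG at −4, VEG-RE would have to gain about 0.55 or 0.13 points. Either is a gain, which goes beyond attenuation.

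**Step 5: separate the two faults.** Repairing only the arithmetic (26 per arm) gives 81% at 4 points but 56% at 3 points. Correcting the sample size therefore does not settle which difference the exercise contrast should be sized on.

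**The case against.** The strongest reply is that attenuation is a directional word and not a design parameter. The programme is 24 supervised progressive sessions with leg press and leg extension, aimed at the measured muscle. A VEG-RE change near zero is a coherent planning value, and a small gain is possible. This stands to the extent that no single low power figure can be pinned on the trial, and the favourable side belongs in the table: 87% at 5 points with 20 per arm. It does not rescue the 80%, because full prevention still gives 69% and the article states no gain.

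A second reply is that the fall from 80% to 69% has nothing to do with attenuation. That is correct. It comes from the two-sided sample size and affects VEG versus OMNI equally. A reader might infer that the attenuation hypothesis alone breaks the power claim; Step 2 shows that it does not.

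Third, the article condenses a fuller protocol that may record an expected VEG-RE change, and the content of the cited studies cannot be checked here. So the statement must be limited to this: the article gives none, and the reasoning it prints concerns diet only.

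Fourth, 19 per arm may be pessimistic. The Discussion says that people who withdraw before the diets start are replaced and that drop-outs are invited to follow-up measurements, and the analysis section allows imputation. Hence the range up to 24.

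**Conclusion.** The point holds in this form: the 80% statement is wrong for the exercise contrast, for two independent reasons. With the plan's own inputs and its two-tailed test, 20 per arm gives 69%, a shortfall shared by both contrasts. Any prevention short of complete lowers power for VEG-RE versus VEG further, to 46% at 3 points or 23% at 2 points. No degree of attenuation reaches 80%; the ceiling is 77%, with all 24 per arm analysed. This rests on the stated 4-point VEG loss, SD 5 in each arm, and the unadjusted two-sided 0.05 level that the section assigns to each contrast.

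Three stronger readings are not supported. A reader might infer that the exercise contrast has only about 23% power, but the share prevented is not given, so only a range can be defended. A reader might ask for the power to win both contrasts, but the plan sets a separate α for each and has no rule that both must succeed. A reader might infer that a null exercise result would be taken as exercise not helping, but nothing in the article plans that interpretation.

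**What to change.** In the sample size section:

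1. Give each primary contrast its own assumed between-arm difference and the basis for it. Say explicitly that OMNI is assumed not to change, and state the expected VEG-RE change.
2. Correct the two-sided derivation: 26 analysed per arm for 4 points and SD 5. Alternatively, keep the numbers and report the power they give.
3. Replace the single 80% statement with two-sided power per contrast over a range of differences at 19 to 24 analysed per arm, as in the table above.
4. If a difference above 4 points is expected because exercise adds volume, say so with its basis, and align the hypothesis in the Introduction and the aim in the Discussion.

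The cost is a few sentences and a small table. No extra participants are needed if the power is restated and not restored. The stated power becomes less favourable: for VEG versus OMNI at 4 points it is 67% to 77% across 19 to 24 per arm, and for the exercise contrast it is at most that under attenuation.

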### Statistical analysis plan

All data will be treated according to the General Data Protection Regulation Act (EU GDPR) and will be collected using Castor EDC [31]. Analyses will be performed in R version 4.1.0. Prior to the analysis, group allocation will be blinded to the members of the research team that will perform the statistical analysis. Descriptive statistics will be used to explore and present baseline characteristics of the study population. Continuous data will be presented quantitatively as means and their 95% confidence intervals or, when not normally distributed, as median [interquartile range]. Categorical data will be presented as counts and percentages. Data will be analysed according to the intention-to-treat principle.

Independent samples t-tests will be performed to analyse the difference in change of thigh muscle volume and the difference in mixed MPS between groups VEG and OMNI and between groups VEG and VEG-RE. Data will be checked for normality using QQ-plots. Missing data may be imputed via multiple imputation or the related data may be eliminated. In case of a non-normal distribution, non-parametric tests will be used or data will be log-transformed. Furthermore, linear mixed models will be used to assess the differences between these groups for the other outcome measures. Participants will be added to the model as random factors. Treatment and timepoint will be added as fixed factors as main effects and their interaction. A maximum of three potential confounding factors may be added to each model as fixed factor. Model assumptions will be checked using QQ-plots and scatterplots. A two-sided p-value < 0.05 will be considered statistically significant. The Benjamini-Hochberg correction will be applied to adjust for multiple testing. In case more than two time points are tested and a significant treatment*time interaction is observed, a post-hoc analysis for will be performed using a Bonferroni correction.

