
Although complex, the design of the Vold-study encompasses the important strength of using several gold standard methodologies, as MRI-scanning, the Biodex measurement, and DEXA-scanning for the assessment of muscle volume, fat distribution, muscle strength and bone mineral density, respectively. Magnetic resonance imaging is considered the gold standard in assessing muscle volume as well as fat distribution [55, 56], and its sensitivity will allow us to pick up small changes over the 12-week intervention period. As such, we envisage that we are able to observe the expected changes within the relatively short timeframe of 12-weeks, whereas a longer study duration would have been needed if less a sensitive measurement method was chosen. The same applies for the Biodex measurement, which is a widely used method to accurately assess muscle strength [57, 58]. Using these high standard methods to assess muscle volume, MFI as well as muscle strength, enables us to gain valuable insights in overall change in muscle quality and function in response to the intervention rather than in muscle volume alone. Loss of muscle strength and function are, in addition to muscle mass, strong predictors for adverse health outcomes and are key characteristics in the identification of sarcopenia [59]. Furthermore, additionally assessing the short-term effects on mixed MPS rates, allows us to investigate to what extent the differences between groups in mixed MPS response translate to the longer term differences in muscle volume. Although the effects of RE on myofibrillar MPS rates correlate well with training induced muscle hypertrophy in trained individuals, it remains to be explored to what extent the acute effects of a dietary intervention on mixed MPS rates translate into longer term adaptations in thigh muscle volume [60, 61].

This 12-week randomized controlled trial aims to assess the effects of a self-composed vegan diet, with or without coinciding RE, on muscle related outcomes and a broad range of other health related outcomes in older adults. The findings will fill major gaps in the literature regarding the health consequences of shifting to a vegan diet later in life, and will provide insights regarding the health implications of the envisaged shift towards more plant-based dietary guidelines.

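### The stated inputs give 69% power at 20 per group, not 80%, and recruiting 24 per group with 20% dropout leaves about 19 (67%).

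*Protocol article*

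**What the plan says.** All inputs are in the Sample size calculation section of the protocol article.

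- **Comparison:** "the sample size calculation was based on testing change in thigh muscle volume between two group comparisons". The two contrasts are vegan versus omnivorous, and vegan versus vegan plus resistance exercise.
- **Error rate:** "A separate two-tailed α-level of 0.05 was used for each contrast".
- **Effect and spread:** "Using an expected mean change of 4% and standard deviation of 5" per cent.
- **Result:** "and 80% power, a total of 60 participants, 20 per group, will need to be included in the study".
- **Dropout:** "Considering a drop-out rate of 20%, 24 participants per group will be recruited, leading to a total of 72 participants".

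The Statistical analysis plan section plans the matching test: "Independent samples t-tests will be performed to analyse the difference in change of thigh muscle volume". It uses the same threshold: "A two-sided p-value < 0.05 will be considered statistically significant". Allocation is 1:1:1 (Randomization section).

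**The concern.** A standardised difference of 0.8 with a two-sided t-test is a familiar case, and it needs about 25 or 26 per group. Twenty is too few. The step from 20 to 24 also looks like multiplication by 1.2, whereas allowing for 20% loss means dividing by 0.8.

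This affects the power claim for the primary outcome. If the claim is wrong, each primary contrast carries a larger risk of missing the planned effect than the article tells its readers. The trial is meant to inform dietary guidelines for older adults, so a non-significant difference has to be read with the true power in view. The Introduction hypothesises only a small loss of muscle volume, and power for differences below 4% is lower still.

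**Working it through.** **Inputs.** Difference Δ = 4%, SD σ = 5%, two-sided α = 0.05, target power 80%, equal groups (Sample size calculation; Randomization). The test is the independent samples t-test (Statistical analysis plan section). The standardised difference is d = Δ/σ = 4/5 = 0.8. This takes the comparator group as unchanged, because no other between-group difference is given.

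**1. Trying to reproduce 20 per group.** The normal approximation is n = 2(z₁₋α/₂ + z₀.₈₀)²/d² per group.

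- Two-sided: 2 × (1.960 + 0.842)²/0.64 = 24.5, so 25 per group.
- One-sided: 2 × (1.645 + 0.842)²/0.64 = 19.3, so 20 per group.

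The stated inputs do not give 20. A one-sided test does by this approximation. By the exact t-test, one-sided power at 20 is 79.9%, so 21 would strictly be needed.

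Other readings do not give 20 either:

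| Reading | Result |
|---|---|
| Paired t-test, d = 0.8 | 15 needed |
| Rank-test efficiency adjustment | 28 to 31 per group |
| Two-sided α of 0.025 per contrast | 31 per group |
| Three-group ANOVA, mean changes 0, −4, 0, total 60 | 72% power |
| Contrast with error pooled over three groups, 20 per group | 70% power |

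**2. Power of the planned test.** Power comes from the noncentral t distribution with 2n − 2 degrees of freedom and noncentrality d√(n/2). At n = 20 the noncentrality is 0.8 × √10 = 2.530, with 38 degrees of freedom and a critical value of 2.024.

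| Evaluable per group | Two-sided power at 4% | Difference detectable with 80% power |
|---|---|---|
| 19 | 67.0% | 4.67% |
| 20 | 69.3% | 4.55% |
| 24 | 77.4% | 4.13% |
| 25 | 79.1% | 4.04% |
| 26 | 80.7% | 3.96% |

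The smallest group size that reaches 80% is 26. For 20 per group to reach 80%, the difference would have to be about 4.55% with SD 5%, or the SD about 4.4% with a 4% difference. The article states neither.

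**3. Dropout.**

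- The plan's figure equals 20 × 1.2 = 24.
- To keep 20 after 20% loss: 20/(1 − 0.2) = 25.
- What 24 leaves: 24 × 0.8 = 19.2, so about 19.
- To keep 26: 26/0.8 = 32.5, so 33 per group and 99 in total.

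**4. Smaller effects and precision.** With 20 per group, power is 46% for a true difference of 3% and 23% for 2%. The expected 95% confidence interval half-width is t × σ × √(2/n) = 2.024 × 5 × √(2/20) = 3.2 percentage points, or 3.3 with 19 per group.

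**The case against.** **The 4% is described as the change in the vegan group, not as a difference.** This is true, and every figure above rests on an unchanged comparator. For the exercise contrast the true difference could go either way: partial attenuation makes it less than 4%, while a net gain makes it more (a 5% difference would give 87% power with 20 per group). But the article says the calculation tested change between two groups and supplies no other difference. Reading the 4% as a within-group change does not help, since a paired test needs 15.

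**The one-sided explanation is a guess.** This stands. The exact one-sided t-test needs 21, so a one-sided calculation is a plausible origin and not an established one. The finding does not depend on it.

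**The dropout slip is small, and 19 is a worst case.** Taken alone it is one participant per group and about 2 points of power. The Discussion says that withdrawals before the diets start are replaced and that dropouts are invited back for follow-up measurements. The Statistical analysis plan section allows multiple imputation. So 67.0% is the planning case, and the best case is 24 evaluable per group. That best case still has only 77.4%.

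**The Discussion's claim about MRI, "its sensitivity will allow us to pick up small changes over the 12-week intervention period", concerns measurement sensitivity, not power.** Largely right. It is not a second instance of the error. It can still be read as saying that the trial will detect small group differences, so a short qualification is reasonable.

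**Nothing says a null result will be read as no effect.** Also right. That is a risk for the report to guard against, not a statement in the plan.

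**Conclusion.** The concern holds. The printed inputs and the printed sample size contradict each other: 20 per group gives 69.3% power, and 80% needs 26. With the plan's own 20% dropout about 19 per group remain, giving 67.0%, and no outcome of recruiting 24 per group reaches 80%. The chance of missing the planned 4% difference is about 31–33% instead of 20%. Most of the shortfall comes from the sample size itself; the dropout step adds a little.

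These figures assume an unchanged comparator, a common SD of 5%, an unadjusted two-sided 0.05 level for each contrast as the Sample size calculation states, and, for the 67.0%, no outcome data from dropouts. For the exercise contrast the figure depends most on the first assumption, because the article gives no expected change under exercise.

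**What to change.** Keep 72 participants and correct the Sample size calculation section. Suggested wording:

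> With 24 participants recruited per group and 20% dropout, about 19 per group will be evaluable. A two-sided independent t-test at 0.05 then has 67% power to detect a 4% between-group difference in change (SD 5%, comparator assumed unchanged). The difference detectable with 80% power is 4.7%.

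Three additions belong with it:

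- State that the 4% is the assumed between-group difference, and for which contrast or contrasts.
- In the Discussion, make clear that the remark on detecting small changes refers to MRI measurement and not to the power of the group comparisons.
- Commit to interpreting both primary contrasts through the estimate and its 95% confidence interval (expected half-width about 3.3 percentage points with 19 per group), so that a non-significant result is not reported as no effect.

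The cost is wording and a less favourable power statement, with no extra participants. This corrects the claim but does not remove the shortfall. If 80% power must be kept under the stated inputs, recruitment would have to rise to 33 per group, 99 in total, which is 27 more than planned.
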